# Impact of fecal microbiota transplantation on chronic recurrent pouchitis in ulcerative colitis with ileo-anal anastomosis: study protocol for a prospective, multicenter, double-blind, randomized, controlled trial

**DOI:** 10.1186/s13063-020-04330-1

**Published:** 2020-06-03

**Keywords:** Fecal microbiota transplantation, Ileal pouch–anal anastomosis, Pouchitis, Randomized controlled trials

## Abstract

**Background:**

Almost 15% of patients with ulcerative colitis (UC) will require a proctocolectomy with ileal pouch–anal anastomosis (IPAA) as a result of fulminant colitis, dysplasia, cancer, or medical refractory diseases. Around 50% will experience pouchitis, an idiopathic inflammatory condition involving the ileal reservoir, responsible for digestive symptoms, deterioration in quality of life, and disability. Though the majority of initial cases of pouchitis are easily managed with a short course of antibiotics, in about 10% of cases, inflammation of the pouch becomes chronic with very few treatments available.

Previous studies have suggested that manipulating the composition of intestinal flora through antibiotics, probiotics, and prebiotics achieved significant results for treating acute episodes of UC-associated pouchitis. However, there is currently no established effective treatment for chronic antibiotic-dependent pouchitis. Fecal microbiota transplantation (FMT) is a novel therapy involving the transfer of normal intestinal flora from a healthy donor to a patient with a medical condition potentially caused by the disrupted homeostasis of intestinal microbiota or dysbiosis.

**Methods:**

Our project aims to compare the delay of relapse of chronic recurrent pouchitis after FMT versus sham transplantation. Forty-two patients with active recurrent pouchitis after having undergone an IPAA for UC will be enrolled at 12 French centers. The patients who respond to antibiotherapy will be randomized at a ratio of 1:1 to receive either FMT or sham transplantation.

**Discussion:**

On April 30, 2014, the World Health Organization published an alarming report on antibiotic resistance. Finding an alternative medical treatment to antibiotics in order to prevent relapses of pouchitis is therefore becoming increasingly important given the risk posed by multiresistant bacteria. Moreover, if the results of this study are conclusive, FMT, which is less expensive than biologics, could become a routine treatment in the future.

**Trial registration:**

ClinicalTrials.gov, NCT03524352. Registered on 14 May 2018.

## Background

As many as 10%–20% of patients with ulcerative colitis (UC; incidence of 24 per 100,000 people annually in Europe) undergo proctocolectomy with ileal pouch–anal anastomosis (IPAA) as a result of refractory disease, dysplasia, or malignancies [1].

Moreover, more than 50% of those who have had an IPAA for a complication brought on by UC will develop an inflammation of the neo-reservoir, known as pouchitis, in the following years. Pouchitis worsens the quality of life, causing disability, an increase in bowel movements, an increased risk of fecal incontinence, abdominal pains, and fever.

The etiology of pouchitis remains unclear. Risk factors, genetic associations, and the serological markers of pouchitis suggest that a close interaction between the host immune response and the pouch microbiota plays a relevant role in the etiology of this idiopathic inflammatory condition [2–4].

While it is known that both host genetics and the microbiome influence the development of pouchitis, precisely how they interact is less well understood. After IPAA surgery, the mucosal structure of the J-pouch becomes more colon-like: villous structures become shallower, mucin expression changes, and the microbial community becomes functionally more similar to a colonic community. Although pouchitis can occur after the construction of pouches for either chronic ulcerative colitis or familial adenomatous polyposis, pouchitis occurs much less frequently in the latter (0%–10%) [5–7], suggesting that pouchitis is less related to the structure of the pouch than it is the patient’s underlying immune dysregulation and the microbiota interacting with the pouch machiels [8]. It is unclear, however, whether pouchitis is a recurrence of UC that manifests itself as the postoperative host ileum and microbiome collectively become more colon-like, or a unique disease with characteristics of both Crohn’s disease (CD) and UC [9, 10].

Inflammatory bowel disease (IBD) has no single etiology, but is rather the consequence of the detrimental interaction between intestinal microbiota, epithelium, and the immune system in genetically susceptible individuals. The use of modern molecular methods that allow a comprehensive analysis of the gut microbiota has shown that patients with IBD have a distorted, low-diversity intestinal microbiota [11, 12]. There is an ongoing debate as to whether changes in the intestinal microbiota precede or follow the development of colitis in IBD. A specific IBD microbiota has, however, yet to be revealed.

Dysbiosis has been indicated as a triggering factor for pouchitis, and this is strongly supported by several lines of evidence pointing to the role played by the microbiota. Pouchitis does not occur before ileostomy take-down and the ileal mucosa’s exposure to the fecal stream. In addition, the pouch effluent contains higher bacterial concentrations than the normal ileum and studies have reported alterations in bacterial colonization after IPAA.

Treatment of pouchitis is largely empirical and only small placebo-controlled trials have been conducted [13, 14]. Antibiotics are the main treatment for acute pouchitis, and metronidazole and ciprofloxacin are the most common initial approaches, often resulting in a rapid response, suggesting that dysbiosis is indeed involved in this pathology [2]. Treatments such as antibiotics and probiotics have a positive effect on the induction and maintenance of remission in pouchitis [15, 16].

While antibiotics are often effective, 5%–15% of patients experience “refractory or recurrent” pouchitis. Active pouchitis may then be divided into acute or chronic, depending on the symptom duration according to ECCO guidelines [13]. The threshold for chronicity is a symptom duration of > 4 weeks. Up to 10% of patients develop chronic pouchitis requiring long-term treatment and a small subgroup have pouchitis refractory to medical treatment. Pouchitis may be classified—according to different perspectives—into: (1) idiopathic versus secondary; (2) in remission versus active; and (3) infrequent (< 3 episodes/year) versus relapsing (> 3 episodes/year). Pouchitis may also be classified based on the response to antibiotic therapy: (1) antibiotic-responsive; (2) antibiotic-dependent (need for continuous antibiotic treatment to maintain remission); and (3) antibiotic-refractory.

Pouchitis recurs in > 50% of patients. Patients with recurrent pouchitis can be broadly grouped into three categories: infrequent episodes (< 1/year); a relapsing course (1–3 episodes/year); or a continuous course. Pouchitis may further be termed treatment responsive or refractory, based on response to antibiotic monotherapy. Although these distinctions are largely arbitrary, they help both patients and physicians when considering management options to alter the pattern of pouchitis [13].

Hence, the definition of our study population as patients in remission on long-term antibiotics has been made according to this ECCO definition.

Note that antibiotics are significantly associated with a high risk of side effects and the risk of multi-resistant bacteria emerging [17].

Recurrent pouchitis or refractory pouchitis is responsible for deterioration in patients’ quality of life—which has already been altered by the surgery itself—increased disability, and in some cases, unfortunately, the need for immunosuppressive medication to avoid further complications with the ileal pouch.

Probiotics (VSL#3®, 450 billion bacteria of eight different strains per gram) are the only treatment to have been found effective in preventing relapse and maintaining remission in patients with chronic pouchitis [18–20].

Probiotics have anti-inflammatory effects and appear to regulate the mucosal immune response through reductions in pro-inflammatory cytokines. Restoring the integrity of the “protective” intestinal mucosa-related microbiota could therefore be one mechanism by which probiotic bacteria function. However, probiotics are not available in all countries and, as they are not considered medication, their cost is not reimbursed. In addition to which, > 50% of patients are not responders. The crucial lack of treatments for these patients explains the need to develop new therapeutic strategies.

The complete substitution of a dysbiotic intestinal microbiota for a “healthy” one is a promising strategy in the treatment of chronic pouchitis. Indeed, fecal microbiota transplantation (FMT), also known as stool transplantation [21], has been shown to be a successful therapeutic approach in other dysbiosis conditions, such as recurrent *Clostridium difficile* infection (CDI), with an overall resolution rate of around 90% and no safety issues in a recent randomized clinical trial [22]. Although the mechanism of efficacy of FMT on CDI is still unclear, FMT is now internationally recommended in cases of recurrent CDI [23]. The only adverse reactions (ARs) reported until 2019 were transitional bowel discomfort, fever, and abdominal pain after 3 years of FMT [24]. Recently, the Food and Drug Administration (FDA) reported two cases of drug-resistant *E. coli* bacterelia transmitted by FMT with one leading to death in two different clinical trials [25]. Both patients were treated with the same donor. It appears that since November 2018 the routine tests for extended spectrum β-lactamase (ESBL)-producing organisms in donor-screening protocol is mandatory.

Given the evidence of the involvement of dysbiosis in the pathogenesis, interest in the use of FMT to treat IBD is growing. In 2017, Paramsothy et al. conducted a meta-analysis of 53 studies (41 on UC, 11 on CD, and four on pouchitis) [26]. Overall, 36% (201/555) of patients with UC, 50.5% (42/83) of those with CD, and 21.5% (5/23) of those with pouchitis achieved clinical remission. Among cohort studies, the pooled proportion achieving clinical remission was 33% (95% confidence interval [CI] = 23–43) for UC and 52% (95% CI = 31–72) for CD, both with a moderate risk of heterogeneity. For four randomized clinical trials (RCTs) in UC, a significant benefit in clinical remission (pooled odds ratio [P-OR] = 2.89, 95% CI = 1.36–6.13, *p* = 0.006) with moderate heterogeneity (Cochran’s Q, *p* = 0.188; I2 = 37%) was noted [27, 28]. A recent Cochrane analysis including either exclusively randomized trials, or non-randomized studies with a control arm, concluded that fecal microbiota transplantation may increase the proportion of participants with UC achieving clinical remission and that there is a need for additional high-quality studies to further define the optimal parameters of FMT [29].

Only nine publications (seven articles and two abstracts) describing two case reports and two open label studies, concerning a total of 62 patients, have been published on the subject of FMT in chronic pouchitis [30–37]. All of them produced heterogeneous results and these studies alone are clearly insufficient to promote this technique. Furthermore, they concerned the treatment of active pouchitis exclusively excepted one study [35] concerning six patients only. There are currently very few available data concerning the efficacy of FMT in the prevention of chronic recurrent antibiotic-dependent pouchitis. Moreover, only 15 RCTs have been published on pouchitis with five studies on chronic pouchitis, including only two on maintaining remission, both using probiotic therapies [14]. All the published studies use a variety of different designs and methods of evaluation and scores, and there is currently a need for additional high-quality trials of pouchitis treatments, especially novel therapies. As already said, the goal of their trials is the remission of active pouchitis. For the first time, the present study will focus on patients in remission to increase this delay, this free interval without treatment. Moreover, the methodology of previous trials is biased, combining refractory and antibiotic-responsive patients [16, 18, 19, 34–36].

Finally, although seven studies are listed on https://clinicaltrials.gov, only one RCT about the use of FMT to treat pouchitis has yet been published [35].

**Table Taba:** 

**Strengths of this study**	
➢ This multicenter study is one of the first randomized placebo-controlled trials assessing the feasibility and clinical efficacy of FMT in the prevention of recurrences of chronic antibiotic-dependent pouchitis.	
➢ This trial is also a double-blind study: all the syringes containing either donor feces in sterile saline and pharmaceutical glycerol, or sterile saline and pharmaceutical glycerol (10%), will be identical and opaque to ensure blinded conditions.	
➢ Patients’ reported quality-of-life measures will be recorded.	
➢ The present study has a long follow-up period (2 years), allowing the patient to be properly monitored.	
➢ The results of the present study could provide new guidelines for the treatment of chronic recurrent pouchitis.	

Finding an alternative treatment to immunosuppressive therapy in recurrent pouchitis is important for patients in order to improve their quality of life, reduce disability, and avoid complications affecting the pouch. Therefore, the aim of the present study was to examine the benefits of FMT in recurrent pouchitis in terms of its ability to prevent relapse and restore the intestinal microbiota. The present study could lead to future non-immunosuppressive treatments for chronic recurrent pouchitis with the current promising development of encapsulated frozen stool.

## Methods/Design

### Study design

This is a prospective, phase III, randomized, double-blind, placebo-controlled, multicenter, national study to evaluate the use of FMT in preventing relapses of pouchitis in patients with UC who have undergone IPAA.

Approximately 50 patients with active recurrent pouchitis after IPAA for UC will be enrolled at 12 expert French centers, with an average of four patients per center. Forty-two of these individuals who have responded after 4 weeks of antibiotherapy will be randomized to receive FMT or sham transplantation at a ratio of 1:1.

### Study population

#### Patients

As mentioned above, no data have been published on the maintenance in remission after FMT in recurrent pouchitis.

There are approximately 80,000 patients with UC in France (EPIMAD register), and as many as 10%–20% will undergo proctocolectomy with IPAA as a result of refractory disease, dysplasia, or malignancies. Approximately 50% of people who have had an IPAA will develop pouchitis in the following years. Most of these patients are monitored in general or university hospitals.

We anticipate that 80% of the patients with chronic recurrent pouchitis will respond to antibiotherapy, with 5% of loss of view. We estimate that each center will include one patient per year (= 0.08 patient/month).

During the screening visit, the study will be fully explained to the patient and informed consent will be obtained if the patient satisfies all inclusion and non-inclusion criteria (Table 1). When giving informed consent, patients will also be asked for permission for the research team to share relevant data with people from the universities taking part in the research or from regulatory authorities, where relevant (the French version of the informed consent is available from the corresponding author on request).

**Table 1 Tab1:** Participant selection criteria

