### Sample size evaluation

This superiority study is designed to have a statistical power of 80% to detect a significant treatment effect on the first onset of pouchitis. We estimate a survival rate of 25% in the control group versus 60% in the treatment group at 6 months (hazard ratio = 0.3685).

These figures are based on the work on probiotics of Gionchetti and Mimura [18, 19].

A total of 32 events are needed to ensure a statistical power of 80%. For a 48-month enrollment period and 24-month follow-up period, 40 patients are needed to observe 32 events. To ensure this statistical power, a total of 42 patients will be randomized.

This sample size calculation takes into account the interim analysis planned at the first 16 observed events.

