### Trial status

The updated protocol was at version 1.2 on June 8, 2018.

The first donor gave their informed consent on December 5, 2018, but did not qualify for donation.

Currently, no patients have been included.

The inclusion period for donors and patients is 48 months, with recruitment scheduled to end in February 2024. The total duration of the study is 76 months, with an anticipated end date of June 2026.

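### As enrolment is described under Study design, the stated accrual and 80% response give about 37–38 randomised patients in 48 months, and the target of about 50 enrolled gives 40, not the stated 42

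*Protocol article*

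**What the plan says.** All references are to the protocol article.

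- **Accrual (Patients).** "We estimate that each center will include one patient per year", also given as 0.08 per month.
- **Response and loss (Patients).** "We anticipate that 80% of the patients with chronic recurrent pouchitis will respond to antibiotherapy, with 5% of loss of view".
- **Enrolment (Study design).** "Approximately 50 patients with active recurrent pouchitis after IPAA for UC will be enrolled at 12 expert French centers", at an average of four per centre. From these, 42 patients who have responded after 4 weeks of antibiotics are to be randomised.
- **Duration (Trial status).** "The inclusion period for donors and patients is 48 months".
- **Size (Sample size evaluation).** "For a 48-month enrollment period and 24-month follow-up period, 40 patients are needed to observe 32 events". The number to be randomised is then set at 42.
- **Abstract, Methods.** "Forty-two patients with active recurrent pouchitis after having undergone an IPAA for UC will be enrolled at 12 French centers", with responders randomised afterwards.
- **Entry state (Table 1, inclusion criterion 6; Table 5).** Patients must have a PDAI below 7 at screening. Screening is at week -2, with existing antibiotics prolonged until 48 hours before transplantation.

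**The concern.** The randomised number should follow from centres, accrual rate, inclusion period and response rate. On the enrolment sequence in Study design, the article's own inputs give fewer than 42. Three different enrolment counts also appear: 42 in the abstract, 48 (four at each of 12 centres) and about 50 in Study design.

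At stake is whether the randomisation target can be met in the stated inclusion period, and whether a reader can trace the 32 events back to a recruitment plan. A shortfall in patients becomes a shortfall in events only to the extent that follow-up does not make up for it.

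**Working it through.** **1. The requirement reproduces.** The 6-month relapse-free rates of 25% and 60% give HR = ln(0.60)/ln(0.25) = 0.3685, as stated. Alpha is not stated; I assume two-sided 0.05. Schoenfeld's formula with 1:1 allocation and 80% power gives 4 × (1.960 + 0.842)² / (ln 0.3685)² = 31.5, so 32 events, as stated. Power at exactly 32 events is 80.6%. The article's event fraction is 32/40 = 0.80. The step from 40 to 42 matches a 5% loss: 40/0.95 = 42.1, or 40 × 1.05 = 42.0. The article does not spell this step out.

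**2. Where the accrual rate is counted.** One patient per centre per year over 4 years is four per centre. Study design gives the same four per centre and attaches it to patients with active pouchitis, before responders are selected. On that description, accrual is counted before the 80% response step.

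**3. The supply.** Randomised = centres × rate × time × 0.80.

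| Basis | Enrolled | × 0.80 | Short of 42 | Short of 40 |
|---|---|---|---|---|
| 12 × 1 per year × 4 years | 48 | 38.4 | 3.6 | 1.6 |
| 12 × 0.08 per month × 48 months | 46.1 | 36.9 | 5.1 | 3.1 |
| Stated target | 50 | 40.0 | 2.0 | 0 |

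**4. What 42 would need.**
- Enrolled: 42/0.80 = 52.5, so 53.
- Time at 12 centres: 52.5 months at one per centre per year (12 per year is 1.0 per month), or 52.5/0.96 = 54.7 months at 0.08 per centre per month.
- Response rate: 42/50 = 84% from 50 enrolled; 42/48 = 87.5% from 48.
- Binomial chance of at least 42 responders when the true rate is 80%: 0.31 from 50 enrolled, 0.13 from 48, 0.03 from 46.

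**5. Effect on power** (Schoenfeld, HR 0.3685, two-sided alpha 0.05 assumed).
- At the plan's 0.80 event fraction: 38.4 patients give 30.7 events and 79.0% power; 36.9 give 29.5 events and 77.4%. For comparison, 42 give 33.6 events and 82.5%.
- With exponential relapse at the stated 6-month rates, captured for the full 24 months, the event probability is 1 − (0.25⁴ + 0.60⁴)/2 = 0.933. Then 36.9–38.4 patients give 34.4–35.8 events and 83–85% power, above the 32 events required.

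**6. The other reading.** If included patients are already in remission on antibiotics, the 0.80 factor drops out. Accrual is then 46.1–48, or 43.8–45.6 after 5% loss, and covers 42.

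**The case against.** The strongest objection is that the shortfall depends on one of two descriptions of entry. Criterion 6 requires remission at screening. Table 5 screens at week -2 and only prolongs antibiotics, so a new 4-week course does not fit between screening and transplantation. On that reading response comes before inclusion, and the stated accrual covers 42. This stands. A reader might infer that no combination of the stated figures produces 42; that would be wrong. But this reading contradicts Study design and the abstract, which enrol active pouchitis, so the text still needs reconciling.

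Second, power rests on 32 events from 40 patients, and 42 appears to include an allowance of about 5%. This stands too. It would be wrong to say that the plan has no contingency, or that a target of 50 fails the event requirement: 50 × 0.80 is exactly 40.

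Third, a reader might conclude that the trial is underpowered. The documents do not support this. The loss is a few points at the plan's own event fraction and disappears if relapses accrue over 24 months. Stopping the count at week 52 would be an added assumption: the unscheduled relapse visit in Table 5 includes PDAI, endoscopy and biopsies, with no week-52 limit. Treating the 5% lost as contributing no events would also overstate the loss, because Statistical methods censors them at their last visit.

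Fourth, these are forecasts, worded as estimates and approximations. That lowers the severity, but rounding does not close a gap of 3.6–5.1 patients out of 42.

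Finally, the abstract's 42 enrolled, read literally, would leave 42 × 0.80 = 33.6 randomised. The other sections consistently say 42 randomised, so this is better taken as loose wording.

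**Conclusion.** The point holds as a moderate correction of consistency and feasibility. On the enrolment sequence in Study design, the stated accrual gives 36.9–38.4 randomised in 48 months, 9–12% below 42 and about 2–3 patients below 40. The target of about 50 gives 40, which meets the stated event requirement but loses the margin above it.

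This rests on accrual being counted before the response step, on the 80% response rate, and on 12 centres recruiting at the stated rate for all 48 months. The power figures also rest on two-sided alpha 0.05, proportional hazards and, for the 24-month case, exponential relapse. They make no adjustment for the interim analysis.

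**What to change.** State one chain from enrolled to responded to randomised to events, with a matching inclusion period. If accrual is counted before response, there are two options:

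- Keep 42 randomised, and state about 53 enrolled and an inclusion period of about 53–55 months at 12 centres. Alternatively, about 14 centres would deliver 42 in 48 months (52.5/4 = 13.1; 13.7 at 0.08 per month).
- Keep 48 months, and state about 37–38 randomised with the events and power that follow. This is below the 40 the article ties to 32 events, so the event fraction and the follow-up it assumes must be stated with it.

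Reconcile the abstract and Study design (active pouchitis at enrolment) with criterion 6 and Table 5 (remission at screening). If patients are included already in remission, remove the 80% step from the accrual chain; 46–48 included then covers 42. In the abstract, describe the 42 as randomised.

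The cost is mainly restated text and figures. The first option also needs a longer inclusion period or more centres; the second needs a slightly lower stated power, or an explicit case that 24-month follow-up supplies the events. The article reports no patients included yet, so the correction can be made before enrolment begins.
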